### Data collection and management

The trial will be coordinated by the Huzhou Third Municipal Hospital, the Affiliated Hospital of Huzhou University, which is responsible for overall study management and coordination across study sites. Data management will be conducted by trained research staff under the supervision of the principal investigator at Peking University. An independent data monitoring committee and endpoint adjudication committee will not be established due to the low-risk nature of the behavioral intervention; however, study progress, protocol adherence, and data quality will be regularly reviewed by the core research team. Any protocol deviations or adverse events will be documented and discussed in regular team meetings. Data quality will be ensured through double-entry and regular audits. Personal data will be kept confidential, and no personal information will be reported.

### Statistical analysis plan

Statistical analyses will be undertaken by an independent statistician, according to a statistical analysis plan developed and signed before database lock. All analyses will use STATA/MP 17.0 or a later version if available.

#### Summary of trial flow and baseline characteristics

Participant flow through the trial will be documented using a CONSORT diagram. The baseline characteristics will be described using summary statistics. Baseline demographic and clinical characteristics will be summarized by group and overall. Continuous variables will be described using means and standard deviations (SD) or medians and interquartile ranges (IQR), as appropriate, while categorical variables will be presented as frequencies and percentages. Baseline values for each outcome variable will be reported at different time points. Comparisons between participants who complete follow-up and those lost to follow-up will be conducted using independent t-tests and chi-square tests to evaluate potential bias.

#### Analysis of the primary outcome and secondary outcomes

The primary outcome (MoCA-B score) will be analyzed using linear mixed-effects models (LMM) within a Difference-in-Differences (DID) framework. All available time points (baseline, week 6, week 12, and week 24) will be included in the primary LMM analysis. Fixed effects will include group, time, and the group-by-time interaction, along with relevant baseline covariates (e.g., age and sex). The DID estimate corresponds to the group-by-time interaction term at week 12, representing the between-group difference in change from baseline to week 12 (the primary endpoint). Short-term (baseline to week 6), long-term (baseline to week 24), and durability effects (week 12 to week 24) will also be explored using the same framework. For secondary outcomes, continuous variables will be analyzed using similar linear mixed-effects models. Binary outcomes will be analyzed using generalized estimating equations (GEE) with a binomial family and logit link. Marginal predicted probabilities will be used to derive risk differences between groups. All analyses will be performed in the intention-to-treat (ITT) population.

Missing outcome data will be handled under the missing-at-random assumption using LMM models, which inherently accommodate incomplete repeated measurements. In addition, a sensitivity analysis will be conducted using multiple imputation with chained equations to assess the robustness of the primary results. Exploratory analyses for all outcomes will also be performed using per-protocol analyses to evaluate efficacy among participants who complete the intervention as specified and provide both baseline and 12-week outcome data. Subgroup analyses will be conducted to explore potential heterogeneity of treatment effects. Two-sided *p*-values of less than 0.05 will be considered to indicate statistical significance.

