### Intervention

#### Intervention group

Participants in the intervention group will receive a 12-week, group-based multicomponent exercise program to be delivered through in-person, face-to-face sessions. Each session will last 30 min and will be conducted twice per week. The multicomponent exercise intervention will consist of five structured components: a warm-up, aerobic training, resistance training, mind–body training, and a cool-down period, forming a complex, theory-informed approach tailored to the physical and cognitive needs of older adults. Participants will be guided by nurses in the nursing home to perform aerobic training, resistance training, and dual-task (mind–body) training throughout the 30-min session. A Rate of Perceived Exertion (RPE) of 5–6, corresponding to moderate intensity, will be recommended. Core aerobic exercises will include shoulder movements, hip abduction or extension, and thigh lifts. Resistance training will consist of functional movements such as squats and trunk twists. Mind–body training will incorporate coordinated activities such as seated marching combined with attention tasks and standing marching paired with inhibition tasks. All participants will be instructed to complete a brief warm-up at the beginning and a cool-down routine at the end of each session to promote safety and recovery.

The intervention will feature a group-based multicomponent exercise program and will be conceptually grounded in the integrated HAPA-TPB model. This theoretical framework was selected to address known facilitators and barriers to exercise engagement among older adults [23], as it incorporates both the motivational phase (e.g., intention formation) and the intenders phase (e.g., planning, execution, maintenance of behavior) and action phase, thereby providing a comprehensive framework for promoting sustainable health behavior change in later life. This integrated model combines the stage-based behavioral pathway of HAPA (preintenders, intenders, and actors) [24, 25] with key motivational determinants from TPB, including attitudes, subjective norms (operationalized as social support in this study), and perceived behavioral control [26]. Particular emphasis was placed on enhancing self-efficacy and peer-based social support as core mechanisms to strengthen adherence and sustain exercise behavior.

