	Enhance outcome expectations	During the introductory session (week 0), participants are informed of potential health benefits, such as improved physical function and cognition. Verbal encouragement and group-based goal tracking are introduced to reinforce progress. Small rewards (e.g., certificates, recognition in group meetings) are given based on attendance and effort
	Enhance subjective norms	At baseline, participants are introduced to peer role models and encouraged to train alongside others in their nursing home. Staff highlight the social benefits and collective identity of participating in the program. Group norms are reinforced by praise and mutual encouragement
	Enhance social support	Sessions are facilitated by a consistent instructor to build trust. Nursing home staff are encouraged to support participants. Peer support is fostered through shared exercises and group discussion
	Enhance attitudes	Educational sessions are held at the start of the intervention, featuring short talks or videos on the benefits of exercise for aging and cognitive health. These are followed by Q&A and small-group reflections to reinforce positive attitudes
**Intender** (from preintenders to intenders)	Action planning	Supervisors work with participants to plan when and how they will attend twice-weekly group sessions. Participants receive a printed plan outlining the frequency, intensity, duration, and type of exercise based on the FITT-VP principle
	Coping planning	Instructors discuss common barriers to participation (e.g., fatigue, joint pain, scheduling) and guide participants through generating coping strategies. Group sharing and encouragement are integrated into each session
	Improve maintenance self-efficacy	Participants are reminded of their ability to maintain training through positive reinforcement, feedback, and group support. Progress charts are displayed to visualize adherence
**Actor (action)**	Enhance recovery self-efficacy	For participants who miss sessions or experience difficulty, instructors provide reassurance and strategies for re-engagement. Group discussion and facilitator check-ins help normalize setbacks
	Reduce risk perception	Facilitators proactively address safety concerns and physical discomfort. Stretching routines, monitoring of vital signs, and individualized modifications are provided to reduce fear of injury

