### Sample size estimation

The sample size was calculated using PASS 2021 software (version 21.0.3). A two-sample independent *t*-test based on effect size was used for estimation, with cognitive function as the primary outcome. Previous studies have reported effect sizes of exercise interventions on cognitive improvement ranging from 0.54 to 2.85 [36–39]. To ensure a conservative estimation, an effect size of 0.54 for cognitive improvement was selected. With a two-sided significance level of *α* = 0.05 and statistical power of 85% (1 − *β* = 0.85), a minimum of 126 participants (63 per group) was required. To account for an anticipated 20% attrition rate, the planned recruitment target was set at 160 participants (80 per group). Due to unavoidable circumstances, such as relocation or death during the recruitment period, 156 participants were ultimately enrolled, which remained sufficient to meet the predefined statistical power requirements.

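### Only the intervention arm is treated in exercise groups, but neither the described primary model nor the sample size allows for within-group correlation; if that correlation is positive, the standard error is too small.

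*Protocol article*

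**What the plan says.** **Allocation and delivery.** Under Randomization and blinding, individuals are allocated 1:1 from a computer-generated list. Under Intervention group: "Participants in the intervention group will receive a 12-week, group-based multicomponent exercise program to be delivered through in-person, face-to-face sessions". Table 2 adds: "Sessions are facilitated by a consistent instructor to build trust". The same section and Table 2 make peer support within the group a core mechanism of the programme. Controls receive routine nursing home care and are not placed in exercise groups.

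**Primary model.** Under Analysis of the primary outcome and secondary outcomes, the article states its method: "The primary outcome (MoCA-B score) will be analyzed using linear mixed-effects models (LMM) within a Difference-in-Differences (DID) framework". The fixed effects are arm, time, arm by time, and baseline covariates such as age and sex; the primary estimate is the interaction at week 12. The only purpose given for the mixed-model structure is to handle incomplete repeated measurements. Random effects are not listed. Binary outcomes use GEE, described only by family and link.

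**Sample size.** Under Sample size estimation: "A two-sample independent *t*-test based on effect size was used for estimation"; "an effect size of 0.54 for cognitive improvement was selected"; "a minimum of 126 participants (63 per group) was required". No ICC or design effect appears.

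**The concern.** This is a partially nested design: individuals are randomised, but one arm is then clustered by its treatment. People who train together under one instructor and are encouraged to influence each other may change in similar ways. If so, each intervention participant carries less independent information than the described model assumes, while controls are unaffected.

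The estimate itself is not biased by this. What suffers is its precision: the standard error of the week-12 interaction is understated, the 95% confidence interval is too narrow, and the test of the average effect rejects too often. A correct analysis would also have less power than the sample size section claims, because that calculation has no allowance for clustering.

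**Working it through.** **Inputs from the protocol article.** Standardised effect 0.54; "two-sided significance level of *α* = 0.05 and statistical power of 85" per cent; 63 per arm; 20% attrition; 78 per arm enrolled.

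**Inputs assumed, because the article gives neither.** Participants analysed per exercise group, m = 6 to 15; ICC of change in MoCA-B within an exercise group, 0.01 to 0.05, with 0.10 as an upper case. With 78 in the intervention arm, these sizes mean about 78/15 ≈ 5 to 78/6 = 13 groups.

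**Step 1: reproduce the plan's figure.** With independent participants, the exact two-sample t-test gives power 0.8468 at 62 per arm and 0.8525 at 63 per arm. So 63 per arm (126) is reproduced, with a design effect of 1. Allowing for attrition, 63/0.8 = 78.75, or 79 per arm (158), in line with the stated target: "To account for an anticipated 20% attrition rate, the planned recruitment target was set at 160 participants (80 per group".

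**Step 2: formulas.** Only the intervention arm's variance is inflated.
- Design effect in that arm: DE = 1 + (m − 1) × ICC.
- Variance ratio, true to assumed: R = (DE + 1)/2.
- Actual two-sided error: 2 × [1 − Φ(1.96/√R)].
- Power of a 5% test that uses the correct standard error: Φ(0.54 × √(n/(DE + 1)) − 1.96).
- Required n per arm: (DE + 1) × ((1.960 + 1.036)/0.54)².

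**Step 3: middle case, m = 10, ICC 0.05.**
- DE = 1 + 9 × 0.05 = 1.45, and R = 2.45/2 = 1.225.
- √R = 1.107, so the described model's standard error is 1 − 1/1.107 = 9.6% too small.
- Actual error: 1.96/1.107 = 1.771, giving 7.7%.
- Power at 63 per arm: 0.54 × √(63/2.45) − 1.96 = 0.778, and Φ(0.778) = 0.782.
- Required n: 2.45 × 30.79 = 75.4, so 76 per arm; 76/0.8 = 95 per arm, 190 in total.

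**Step 4: range.**

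| m | ICC | DE | R | SE too small by | Actual error | Power, 63 per arm | n per arm | Total with 20% attrition |
|---|---|---|---|---|---|---|---|---|
| 6 | 0.01 | 1.05 | 1.025 | 1.2% | 5.3% | 0.849 | 64 | 160 |
| 10 | 0.05 | 1.45 | 1.225 | 9.6% | 7.7% | 0.782 | 76 | 190 |
| 15 | 0.05 | 1.70 | 1.35 | 13.9% | 9.2% | 0.742 | 84 | 210 |
| 15 | 0.10 | 2.40 | 1.70 | 23.3% | 13.3% | 0.642 | 105 | 264 |

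At ICC 0, R = 1, the error is 5% and power by the same normal approximation is 0.858. These are large-sample figures; with few groups, the loss of degrees of freedom makes matters somewhat worse.

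**Step 5: reserve.** 78 × 0.8 = 62.4, so about 62 per arm remain at the planned attrition. Power is then 0.847 with independence and 0.775 in the middle case. If all 78 per arm were analysed, the middle case would give 0.861.

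**The case against.** **The article is silent on random effects.** Its list covers fixed effects only, and it gives no random-effects structure at all, not even a participant term. An exercise-group term would sit in that undescribed part, and the analyses follow a separate plan to be signed before database lock. A reader might infer that the trial's standard error is certainly too small; the article does not establish that. What stands is that the model as described makes no provision for groups, and that the sample size is fixed on independence.

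**The size is assumed.** Group size, number of groups, number of instructors and ICC are all absent. The relevant ICC is for change from baseline to week 12, which need not equal the ICC for MoCA-B level. If the programme did nothing for anyone, there would be no treatment-induced clustering; the excess error arises when groups differ in benefit while the average benefit is nil. This stands, so only a range can be given. It does not remove the problem for the confidence interval, which is too narrow whenever the ICC is positive.

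**Three stronger readings are not supported.**
- A missing nursing-home term does not by itself shrink the standard error. Allocation is individual, and where a home contains both arms, shared home effects tend to cancel in the comparison.
- A positive result would not be false because it came partly from the group or instructor. Both are intended parts of the intervention; the issue is variance, not what is being estimated.
- GEE for the binary outcomes is not wrong. Replacing it with a mixed logistic model would be a preference.

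**Conclusion.** The point holds conditionally. The design creates clustering in one arm, the sample size ignores it, and the primary model as described does not account for it. For any positive within-group ICC of change, that model understates the standard error. Under the assumed 6 to 15 per group and ICC 0.01 to 0.05, the understatement is about 1% to 14% and the actual error rate about 5.3% to 9.2%. In the middle case, power falls to about 78% at 63 per arm. The 13.3% error rate needs both the largest group and ICC 0.10, and should not be read as the expected size. Because the planned attrition leaves about 62 per arm, there is little room to absorb a design effect. This should be settled before the analysis plan is signed; it does not invalidate the trial.

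**What to change.** - **Primary model.** Add a random exercise-group effect acting only in the intervention arm, with each control as a singleton, alongside the participant-level repeated-measures structure. Use Satterthwaite or Kenward-Roger degrees of freedom, because groups will be few.
- **Binary outcomes.** Keep the GEE, but cluster the robust variance on exercise group (controls as singletons) with a small-sample correction.
- **Data and reporting.** Record an exercise-group identifier, presumably recoverable from the adherence records. State the number and size of groups and the number of instructors, and report the estimated ICC.
- **Sample size.** Restate power over a range of ICC.

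A nursing-home term is optional. If one instructor led every session, that effect cannot be separated from arm by any model term, and the report should say so.

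The cost is analysis-plan wording and one variable; trial conduct does not change. The confidence interval will be wider if the ICC is positive, and the stated power will be less favourable.

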### Measurements

#### Primary outcome measures

All outcome data will be collected through a face-to-face electronic questionnaire system administered by trained physicians or nurses who have received standardized training. The primary outcome is cognitive function measured by the Montreal Cognitive Assessment-Basic (MoCA-B) score. The MoCA-B is a validated screening tool specifically developed to detect mild cognitive impairment (MCI) in individuals with limited educational backgrounds or illiteracy [27, 28]. It evaluates a range of cognitive domains, including executive function, immediate and delayed recall, verbal fluency, orientation, calculation, abstraction, visuoperception, and naming. The assessment takes approximately 15 min to complete and is scored out of a maximum of 30 points. To reduce potential bias related to education and literacy, one point will be added to the total score for participants with fewer than 4 years of education or those identified as illiterate (defined as the inability to read or write fluently in daily life), provided their raw score is below 30.

MoCA-B will be assessed at baseline, 6 weeks, 12 weeks, and 24 weeks post-randomization. The primary endpoint is defined as the between-group difference in change from baseline to 12 weeks post-randomization (end of the intervention period). Results will be presented as adjusted mean differences with 95% confidence intervals. All primary analyses will follow the intention-to-treat principle.

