#### Secondary outcome measures

Secondary outcomes include Quality of Life measured by the EuroQol-5D-5L (EQ-5D-5L), Activities of Daily Living (ADL), Pittsburgh Sleep Quality Index (PSQI) [29], intrinsic capacity, frailty, social support, and intervention cost and benefit, which have been validated among Chinese older adults. Intrinsic capacity will be evaluated in accordance with the WHO Integrated Care for Older People (ICOPE) guidelines [30], across the following domains: cognitive capacity assessed by MoCA-B, vitality assessed using Mini Nutritional Assessment–Short Form (MNA-SF), locomotion measured by Short Physical Performance Battery (SPPB), psychological status assessed using Patient Health Questionnaire (PHQ-9) [31], and sensory determined by self-reported vision and hearing questions. Frailty will be assessed using the frailty phenotype (FP) [32, 33], physical activity levels will be evaluated using the International Physical Activity Questionnaire–Short Form (IPAQ-SF), and social support will be assessed by the Lubben Social Network Scale (LSNS) [34].

Secondary outcomes will be assessed at baseline, 6 weeks, 12 weeks, and 24 weeks post-randomization. Secondary endpoints will be defined as the between-group differences in change from baseline at each post-randomization timepoint. Results will be reported as adjusted mean differences or risk differences with corresponding 95% confidence intervals, as appropriate to the outcome type. All secondary analyses will follow the intention-to-treat principle.

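### The effect is promised as an adjusted mean difference, but age and sex entered without a time interaction cancel, exactly or nearly, from the week-12 group-by-time term

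*Protocol article*

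**What the plan says.** Under Primary outcome measures, the target is a difference in change: "The primary endpoint is defined as the between-group difference in change from baseline to 12 weeks post-randomization". The form of reporting follows: "Results will be presented as adjusted mean differences with 95% confidence intervals". Under Secondary outcome measures the same label is used: "Results will be reported as adjusted mean differences or risk differences with corresponding 95% confidence intervals, as appropriate to the outcome type".

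Under Analysis of the primary outcome and secondary outcomes, the model is set out in three statements:

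- Response rows: "All available time points (baseline, week 6, week 12, and week 24) will be included in the primary LMM analysis". Baseline MoCA-B is therefore an outcome value, not a covariate.
- Fixed effects: "Fixed effects will include group, time, and the group-by-time interaction, along with relevant baseline covariates (e.g., age and sex"). The only interaction named is group by time.
- Effect to be reported: "The DID estimate corresponds to the group-by-time interaction term at week 12".

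Incomplete cases stay in the model: "Missing outcome data will be handled under the missing-at-random assumption using LMM models". Multiple imputation is added as a sensitivity analysis. Continuous secondary outcomes are to use similar mixed models. A separate analysis plan is to be signed before database lock; it is not shown.

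**The concern.** The label and the model do not fit together. Age and sex at baseline do not change between visits. If they enter as plain fixed effects, they explain differences in the level of MoCA-B between people. The endpoint is a change, and a term that is the same at every visit cannot alter a change.

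Readers who see an adjusted difference will assume that chance imbalance in predictors of cognitive change has been dealt with. They will also assume that dropout related to those covariates has been allowed for. Under the model as it reads, little of either happens. The same holds for every continuous secondary outcome analysed this way.

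**Working it through.** **1. The plan's own figure.** For a standardised effect of 0.54, two-sided alpha 0.05 and 85% power, the exact noncentral t gives 84.7% power at 62 per arm and 85.25% at 63. The stated 63 per group (126) is reproduced. Inflating for attrition, 63/0.8 = 78.75 per arm; 78 per arm were randomised. Nothing below changes these figures.

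**2. The algebra with complete data.** Write the score of person i at visit j as

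Y_ij = μ_j + γ_j·g_i + β·x_i + (random effect and error),

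where g is the arm and x a time-constant covariate. Because group by visit is saturated, the fitted arm difference at visit j is

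γ̂_j = (Ȳ_1j − Ȳ_0j) − β̂·(x̄_1 − x̄_0).

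The correction β̂·(x̄_1 − x̄_0) carries no index j. The reported term is γ̂_12 − γ̂_0, so the correction subtracts out and leaves the raw difference in mean change. This holds for any covariance matrix common to all persons.

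**3. Numbers put in.** Table 3 gives mean ages 68.63 and 69.76, so x̄_1 − x̄_0 = −1.13 years. With an assumed slope of −0.08 points per year, the correction is −0.08 × −1.13 = 0.09 points at baseline and 0.09 points at week 12; the net correction to the change is 0. If the slope could differ by visit, an assumed extra −0.04 points per year after baseline would give −0.04 × −1.13 = 0.045 points. That correction is available only with an age-by-visit term.

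**4. Numerical check.** In one example with complete data, generalised least squares gave 1.0518 without covariates, 1.0518 with age and sex main effects, and 1.0518 as the raw difference in mean change. This was so under both compound symmetry and an unstructured covariance. With age-by-visit and sex-by-visit terms it gave 1.0238.

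**5. With attrition.** A person without a week-12 visit contributes to the baseline rows only, so the covariate means behind the two visits differ and the cancellation is no longer exact. Its size was found by simulation.

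Inputs from the article: 78 per arm, four visits, 20% attrition, and age means and SDs by arm.

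Assumed, because the article does not give them:
- between-person SD 1.6 and residual SD 1.5, so √(1.6² + 1.5²) = 2.19, close to the baseline SDs of 2.32 and 2.19;
- effect 1.2 points;
- age slope −0.08 per year and sex effect 0.5;
- extra post-baseline age slope 0 or −0.04 per year.

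The complete-data standard error implied by these values is √(4 × 1.5²/78) = 0.340. There were 40 simulated trials per row, fitted by REML with a random intercept.

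| Setting | Main effects vs no covariates: mean (largest) absolute shift | Covariate-by-visit vs no covariates: mean absolute shift | SE: none / main / by-visit |
|---|---|---|---|
| Complete, extra slope 0 | < 1e-13 | 0.027 | 0.338 / 0.338 / 0.342 |
| Complete, extra slope −0.04 | < 1e-13 | 0.062 | 0.341 / 0.341 / 0.342 |
| 20% random dropout, extra slope 0 | 0.013 (0.051) | 0.047 | 0.368 / 0.367 / 0.373 |
| 20% random dropout, extra slope −0.04 | 0.017 (0.063) | 0.083 | 0.371 / 0.370 / 0.373 |
| Dropout depends on age differently by arm, extra slope −0.04 | 0.050 (0.119) | 0.138 | 0.366 / 0.365 / 0.370 |

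A separate set of 60 trials per setting, with education added, gave mean shifts of 0.007 and 0.011 from main effects under 20% loss. Further runs with arm-dependent dropout gave 0.05–0.07 on average and up to 0.19.

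Against a standard error near 0.37, the main-effects shift averages 0.013/0.37 = 4% to 0.050/0.37 = 14% of a standard error. In the last row the mean estimates were 1.403 (no covariates), 1.353 (main effects) and 1.272 (by-visit). Main effects recover 0.050 of the 0.131-point movement; the other 0.081 needs the by-visit terms.

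**The case against.** **The text does not say main effects only.** The covariate list is open, the form of entry is not spelled out, and an unseen analysis plan may add interactions. A reader might infer that the article rules out covariate-by-visit terms; it does not. What stands is narrower. The article itself fixes the reported term, the response rows and the label, and it names one interaction. Main effects are the natural reading. The open list is no rescue: any time-constant covariate entered this way cancels too. That includes near vision, for example, which is good in 2.56% against 14.10% in Table 4.

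**The cancellation is not exact in this trial.** This is correct. A reader might infer that the reported figure will be identical to the unadjusted one. That is so only with complete follow-up, and the article expects 20% attrition. If dropout depends on age differently by arm, the shift is not negligible in every data set.

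**There is no bias and no loss of power.** This largely stands. Under randomisation the unadjusted difference in change is a valid estimate, and its interval already allows for chance imbalance. Covariate-by-visit terms left the standard error within about 1.5%. The shifts in the table are mostly chance movement in either direction. The observed age gap is small (p = 0.434), and sex is nearly balanced (55 against 53 women). A reader might infer a biased or underpowered primary analysis; the documents do not support that.

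**The label is customary, and imputation is planned.** An estimate from a model containing covariates is often called adjusted, and the model is openly described. Covariates can also inform the imputation. Neither point makes the primary estimate adjusted for predictors of change.

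**Conclusion.** The point holds as a mismatch between label and model. On the natural reading, the week-12 group-by-time term equals the unadjusted difference in change with complete data. With the expected attrition it differs by about 0.01–0.02 points under random dropout and 0.05–0.07 on average under arm-dependent, age-related dropout, against a standard error near 0.37. The effect is adjusted largely in name only, in the primary analysis and in the continuous secondary ones.

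The complete-data result is algebra and needs no assumption beyond the stated model with a common covariance. The attrition figures rest on the assumed variances, slopes and dropout patterns. Letting the covariates act on change moves the estimate by roughly 0.03–0.14 points under those assumptions. What is gained is that adjustment for chance imbalance and covariate-dependent dropout takes effect. Precision is essentially unchanged, and the sample size is not affected.

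**What to change.** Under Analysis of the primary outcome and secondary outcomes, and in the analysis plan before it is signed:

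- State that the prespecified baseline covariates, age and sex, enter with covariate-by-visit terms in the primary model and in the models for continuous secondary outcomes.
- Define the adjusted mean difference as the week-12 group-by-time term from that model.
- Report the same term from the model without covariates beside it.

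Education by visit may be added, since the eligibility bands depend on education, but it is optional.

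If the covariates are kept as main effects only, remove the word *adjusted* from the description of the mean differences under Primary outcome measures and Secondary outcome measures.

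The cost is one sentence and no new data. With four visits, each covariate adds three parameters, so age and sex add 2 × 3 = 6, which is minor with 156 participants.
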